## Abstract

**Background:**

Given the increasing prevalence of diabetes and the lack of patients reaching recommended therapeutic goals, novel models of team-based care are emerging. These teams typically include a combination of physicians, nurses, case managers, pharmacists, and community-based peer health promoters (HPs). Recent evidence supports the role of pharmacists in diabetes management to improve glycemic control, as they offer expertise in medication management with the ability to collaboratively intensify therapy. However, few studies of pharmacy-based models of care have focused on low income, minority populations that are most in need of intervention. Alternatively, HP interventions have focused largely upon low income minority groups, addressing their unique psychosocial and environmental challenges in diabetes self-care. This study will evaluate the impact of HPs as a complement to pharmacist management in a randomized controlled trial.

**Methods/Design:**

The primary aim of this randomized trial is to evaluate the effectiveness of clinical pharmacists and HPs on diabetes behaviors (including healthy eating, physical activity, and medication adherence), hemoglobin A1c, blood pressure, and LDL-cholesterol levels. A total of 300 minority patients with uncontrolled diabetes from the University of Illinois Medical Center ambulatory network in Chicago will be randomized to either pharmacist management alone, or pharmacist management plus HP support. After one year, the pharmacist-only group will be intensified by the addition of HP support and maintenance will be assessed by phasing out HP support from the pharmacist plus HP group (crossover design). Outcomes will be evaluated at baseline, 6, 12, and 24 months. In addition, program and healthcare utilization data will be incorporated into cost and cost-effectiveness evaluations of pharmacist management with and without HP support.

**Discussion:**

The study will evaluate an innovative, integrated approach to chronic disease management in minorities with poorly controlled diabetes. The approach is comprised of clinic-based pharmacists and community-based health promoters collaborating together. They will target patient-level factors (e.g., lack of adherence to lifestyle modification and medications) and provider-level factors (e.g., clinical inertia) that contribute to poor clinical outcomes in diabetes. Importantly, the study design and analytic approach will help determine the differential and combined impact of adherence to lifestyle changes, medication, and intensification on clinical outcomes.

**Trial registration:**

ClinicalTrials.gov identifier: NCT01498159

## Background

Individuals with diabetes are at greater risk for cardiovascular disease, the leading cause of death among men and women [1]. To reduce the risk of cardiovascular disease, attentive management of blood glucose, blood pressure, and LDL-cholesterol levels is paramount. Despite available treatments, less than 10-20% of people achieve their goals in therapy [2-7]. While time-trend analyses show improvement in blood glucose, blood pressure, and cholesterol control, African-Americans and Latinos have worse control of these risk factors compared with Whites [8-13]. These differences in intermediate factors may contribute to higher complication rates in minority groups, such as renal disease, coronary artery disease, and amputations, as well as mortality [9,14,15].

In order for most individuals to reach their goals in therapy, regular, ongoing adherence to medication is required. Common factors that contribute to non-adherence include low health literacy, depression, lack of medication knowledge, lack of social support, concerns about adverse events and dependency, poor patient-clinician communication, and limited access to healthcare resources [16,17]. In the Latino population, additional barriers may include low English proficiency, cultural issues, and poorer access to conventional healthcare. Additionally, low adherence may reduce treatment modifications and intensification [18,19].

From the healthcare provider perspective, intensification of medication therapy is often limited by “clinical inertia,” which occurs when providers fail to appropriately intensify therapy in patients despite recognizing elevations in blood glucose, blood pressure, or cholesterol [20]. Clinical inertia is sometimes related to providers having limited time allotted for each encounter and patients presenting with concerns that compete for attention [20]. In addition, providers are often not trained in the complex array of psychosocial or environmental factors that affect adherence which must be addressed prior to intensification of medication [21].

Given the increasing prevalence of diabetes and the lack of patients reaching recommended therapeutic goals, novel models of team-based care are emerging. These teams typically include physicians, nurses, case managers, pharmacists, and community-based peer health promoters (HPs) [17,22-24]. Recent evidence supports the role of office-based clinical pharmacists in diabetes management to improve glycemic control, as they offer expertise in medication management with the ability to collaboratively intensify therapy [25-27]. Such pharmacists are often found in primary care teams providing diabetes management [28,29].

Community-based health promoters may further enhance the effectiveness of clinical pharmacists in medication management [17]. Health promoter interventions have focused largely upon low income minority groups, addressing their unique psychosocial and environmental challenges in diabetes self-care. Health promoters can perform home visits and telephone calls to provide education, evaluate medication use, promote behavioral change and self-management, and reinforce pharmacist and other provider recommendations. Such measures may improve medication adherence and support intensification to reach goals in blood sugar, blood pressure, and cholesterol.

Building upon a pilot study, the present study was designed to determine the effectiveness of pharmacist-health promoter team management in addressing medication adherence and intensification [17]. In addition, the study will investigate the benefit derived from adding HP support following receipt of clinical pharmacist services, and maintenance of improved behaviors and outcomes after phasing out health promoter support. Finally, cost and cost-effectiveness of this team approach will be examined.

## Materials/Design

### Objectives

Our primary goal is to evaluate the effectiveness of pharmacist plus health promoter support (*Pharmacist+HP*) compared with pharmacist alone (*Pharmacist*) on diabetes behaviors (including healthy eating, physical activity, and medication adherence), hemoglobin A1c, blood pressure, and LDL-cholesterol levels among African-American and Latino adults with uncontrolled type 2 diabetes. Secondarily, we will evaluate the maintenance of improved diabetes behaviors, as well as clinical outcomes, by phasing out health promoter support from the *Pharmacist+HP* group after one year. Also, we will evaluate the intensification offered by adding a health promoter after one year of Pharmacist alone. Finally, we will determine the cost and cost-effectiveness of the *Pharmacist+HP* and *Pharmacist* alone approaches.

### Study design

The proposed study is a randomized trial with crossover after one year (Figure 1). Three hundred African-American and Latino patients with uncontrolled type 2 diabetes will be randomized to receive either:

1. *Pharmacist*: Clinical pharmacists will provide medication and disease management services to patients following a Pharmacist Management Protocol.

2. *Pharmacist+HP*: Includes clinical pharmacist services, plus a health promoter who will attend to both lifestyle and medication adherence-related issues by identifying barriers, solving problems, and providing support through home visits and telephone contact.

**Figure 1 F1:**
[figure not shown]
**Study Design.** The proposed study is a randomized trial with crossover after one year. Three hundred African-American and Latino patients with uncontrolled type 2 diabetes will be randomized to receive either *Pharmacist* or *Pharmacist+HP* conditions. After one year, groups will crossover. The *Pharmacist* group will be intensified by adding health promoter support. Concurrently, maintenance will be evaluated in the *Pharmacist+HP* group by phasing out health promoter support.

After one year, groups will crossover. The *Pharmacist* group will be intensified by adding health promoter support. Concurrently, maintenance will be evaluated in the *Pharmacist+HP* group by phasing out health promoter support. Outcomes in terms of medication adherence, A1c, blood pressure, and LDL-cholesterol levels will be evaluated at 0, 6-, 12- and 24-months.

### Ethics

The research protocol has been approved by the University of Illinois at Chicago Institutional Review Board (2011–0099).

### Study population and site

The University of Illinois Medical Center (UIMC) includes both inpatient and outpatient facilities serving a diverse, low-income population in Chicago. There are approximately 8,000 unique African American or Latino individuals receiving care for diabetes in the outpatient setting annually. The UIMC has multiple off-site ambulatory centers staffed by Family Practice and Internal Medicine primary care physicians (PCPs), and include affiliated Federally Qualified Health Centers (FQHCs). We anticipate participation of 6–8 clinical entities in the study. All sites share access to the electronic medical record (EMR), Cerner Powerchart (Cerner Corporation, Kansas City, MO).

### Inclusion criteria

Patients will be eligible for the study if they: (a) are self-identified as Latino/Hispanic or African-American; (b) have verbal fluency in English or Spanish; (c) are age 21 or above; (d) have a history of type 2 diabetes; (e) have an elevated A1c level 8% or higher in the past year (confirmed through EMR); (f) received primary care at UIMC for at least one year; and (g) take at least one oral medication for diabetes or hypertension (for adherence assessment).

### Exclusion criteria

Patients will be excluded from the study if they: (a) are unable to verbalize comprehension of study or have evidence of impaired decision making (e.g., dementia); (b) live outside of the Chicago area three or more months of the year; (c) have a household member already participating in same study; (d) plan to move from the Chicago area within the next year; or (e) are pregnant or trying to become pregnant.

### Identification, recruitment, and randomization of participants

The recruitment process will be carried out separately for each ambulatory site as determined by the project coordinator and clinical staff. On-site research assistants (RAs) will receive referrals from staff or patients interested in being screened for the study. All participant medical records are reviewed by a study physician to ensure A1c eligibility. Individuals deemed eligible will be scheduled for an appointment at the university Clinical Interface Core facility to complete written consent, HIPAA authorization, and baseline data collection. The RAs will inform patients that the research is being conducted to improve medication management in diabetes care and to find out whether pharmacists and health promoters help people reach goals of therapy. The RAs will spend additional time discussing the study protocol in detail as part of consent procedures and use the “teach-back” method to ensure participant comprehension [30].

Randomization to receive either *Pharmacist* or *Pharmacist+HP* assignments for the first year will occur after consent and completion of all baseline data collection. A random sequence of 300 participant assignments will be used. Blocked randomization will ensure that allocation to experimental conditions will be balanced within four gender by ethnicity subgroups at each site. The project coordinator will independently determine group assignments and will log the information separately. Baseline results for A1c and fasting lipid profile are entered into the patient’s medical record by a study physician and electronically shared with the primary care physician and pharmacist.

### Sample size calculation

Sample size calculations are powered to detect change in A1c. Based on a previous study [31], we estimated a mean baseline A1c level of 10.0% with standard deviation of 1.8% and an effect size of (1.0/1.8) 0.56. The cross-time correlation was estimated to be 0.30. We adjusted for clustering, assuming an intraclass correlation coefficient (ICC) of 0.02 and cluster size of 30, which yields a design effect of 1.58. Two-sided alpha of 0.05 and 80% power are assumed requiring a minimum of 114 per group. Allowing for an estimated 10% drop-out during each of the two years, approximately 150 patients will be required for each group (or 300 total).

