### Data analyses

Data will be analyzed for clinical effectiveness using intention-to-treat principles [32-34]. To represent dropouts in the analysis, missing data will be imputed using various approaches, such as “last value carried forward.” The Little and Yau “return to baseline” imputation rule, in which any gains over baseline levels dissipate upon dropout, will be used for primary analyses. Patients who share a single primary care physician (PCP) or health promoter (HP), might exhibit similarities that are not shared with patients attended to by other physicians. To address this, we will include random effects in the model for clinic site, PCP, and HP. We will include as predictors relevant care and treatment-related variability such as medication therapy intensifications and clinical encounter frequency.

We will test the hypothesis that A1c, blood pressure, and LDL-cholesterol levels will be lower and diabetes behaviors (including medication adherence) will be improved with patients receiving *Pharmacist+HP* compared with those receiving *Pharmacist* alone. Univariate comparisons between the two study groups with respect to outcome measures and covariates at baseline will be conducted using Chi-square tests for categorical variables, Kruskal-Wallis tests for ordinal variables, and linear mixed models for continuous variables. Non-normal continuous data will be transformed prior to linear model analyses. The baseline variables include demographic, therapy complexity, and health literacy data. If we find any between-group differences at baseline, we will adjust for this in our primary multivariate analyses by including relevant covariates.

We will also extend the usual analysis of crossover designs by including a longitudinal trend component in the first year. Thus, we can examine the time course (0, 6, and 12 months) as linear or quadratic over the first three measurements. This will allow us to investigate whether changes are made early, and at what rate they continue through the rest of the time period. This analysis permits the comparison of trends between *Pharmacist* and *Pharmacist+HP* conditions. In addition, we will regard participants as a random effect and will use Gaussian mixed-model estimations (SPSS MIXED command). We can then substitute treatment by period interactions for the carry-over effects, and the model can be reduced in a recommended sequence (first omit carry-over, then omit treatment, finally omit period).

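### The sample size rests on an unadjusted change in A1c at r = 0.30, and baseline is adjusted for only if the arms differ; adjusting unconditionally would cut variance by about 35% at no cost in patients

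*Protocol article*

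**What the plan says.** Protocol article, Sample size calculation: "Sample size calculations are powered to detect change in A1c". The inputs are "standard deviation of 1.8% and an effect size of (1.0/1.8) 0.56", a correlation ("The cross-time correlation was estimated to be 0.30") and clustering, "assuming an intraclass correlation coefficient (ICC) of 0.02 and cluster size of 30, which yields a design effect of 1.58". The result is "Two-sided alpha of 0.05 and 80% power are assumed requiring a minimum of 114 per group", raised to about 150 per group for dropout.

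Protocol article, Data analyses: the hypothesis is worded in terms of lower A1c, blood pressure and LDL levels, and the primary analysis of each outcome is placed in a general linear mixed model framework. A first-year trend component is added: "Thus, we can examine the time course (0, 6, and 12 months) as linear or quadratic over the first three measurements". Trends are then compared between arms, with participants as a random effect. The arms are to be compared at baseline on outcome measures and covariates, and the primary analysis is adjusted only where a difference turns up. Dropouts are handled in the primary analysis by a return-to-baseline imputation.

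The section on identification, recruitment and randomisation places randomisation after all baseline data have been collected.

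**The concern.** Baseline A1c can be ignored, subtracted or adjusted for. Subtraction beats ignoring it only when the correlation exceeds 0.5, and adjustment is at least as efficient as either. The protocol's own r of 0.30 lies well below 0.5, yet the sample size uses subtraction.

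The analysis text does not recover the loss. Its one stated rule for baseline adjustment depends on an observed imbalance, so the precision gain is given up whenever the arms look alike. Because randomisation follows baseline measurement, any baseline difference is chance, and adjustment needs no trigger. At stake is precision that the collected data already offer. The quoted 80% power also describes a less efficient estimator than the trial could use.

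**Working it through.** **Inputs** (Sample size calculation): difference 1.0, SD 1.8, r = 0.30, two-sided alpha 0.05, power 80%, ICC 0.02, cluster size 30. Equal SDs at both times and the same design effect for every analysis are assumed.

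**Design effect:** 1 + (30 − 1) × 0.02 = 1.58, as stated.

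**Formula:** n per group = 2 × (1.96 + 0.8416)² × f × (1.8/1.0)² × 1.58, where f is the variance factor of the analysis.

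| Analysis | f | n before clustering | × 1.58 |
|---|---|---|---|
| Change from baseline | 2(1 − r) = 1.40 | 71.2, so 72 | 113.8, so 114 |
| Follow-up only | 1.00 | 50.9, so 51 | 80.6, so 81 |
| Baseline-adjusted | 1 − r² = 0.91 | 46.3, so 47 | 74.3, so 75 |

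The first row reproduces the stated 114. A t-based calculation (72.18 × 1.58 = 114.0) agrees, and using 0.56 in place of 1.0/1.8 changes the figure by less than 3%. The other two rows do not come near 114.

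**Size at 114 per group.** The standard error is 1.8 × √f × √(2 × 1.58/114).
- f = 1.40: SE 0.355, power for 1.0 point 80.5%, difference detectable with 80% power 2.8016 × 0.355 = 0.99.
- f = 1.00: power 91.6%, detectable difference 0.84.
- f = 0.91: SE 0.286, power 93.8%, detectable difference 0.80.

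The variance reduction from change score to adjustment is 1 − 0.91/1.40 = 35%.

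**Dependence on r.** The ratio of change-score to adjusted variance is 2(1 − r)/(1 − r²) = 2/(1 + r). This is 1.54 at r = 0.30, 1.33 at 0.5 and 1.18 at 0.7. The direction is the same for every r below 1.

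**Return-to-baseline imputation.** Take 10% dropout by 12 months and no mean change. Imputed dropouts have zero change, so the change-score factor is 0.9 × 1.40 = 1.26. The correlation becomes 0.9 × 0.30 + 0.1 × 1 = 0.37, so the adjusted factor is 1 − 0.37² = 0.863. The excess is 1.26/0.863 = 1.46, or about 46%. If both arms fall by 1.0 point on average (an assumption), both factors gain 0.1 × 0.9 × (1.0/1.8)² = 0.028. The ratio is then 1.288/0.891, about 1.45.

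**The 0/6/12-month trend model.** With three equally spaced visits, compound symmetry and a separate intercept for each arm, the fitted linear change to 12 months uses only the 12-month value minus baseline. A quadratic fits three points exactly, so its 12-month contrast is the same quantity. Both have factor 1.40. An AR(1) structure with r = 0.30 between baseline and 12 months also gives 1.40. With r = 0.30 between adjacent visits it gives 1.82, against 0.99 for adjustment. If the arms are constrained to one baseline mean under compound symmetry, the factor is 0.91 (quadratic) or 0.85 (linear).

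**The case against.** The sample size contains no error. It reproduces, and sizing on change while analysing more efficiently would be conservative.

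A reader might infer that the planned analysis is itself a change-score comparison. The protocol article does not say so. The hypothesis is worded on levels, the trend model is offered as an extension, and the primary analysis is fixed only as a general linear mixed model. The 1.40 factor for the trend model requires free group intercepts, which are a usual default but are not stated. Nor is every group-by-time term the 12-month change: the quadratic component is Y0 − 2·Y6 + Y12. A reader might also take the 54% to mean that the trial recruits too many or too few patients; it supports neither.

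It can also be said that the handling of baseline belongs in an analysis plan that is not shown. This would hold if the article were silent, but it states a rule, and that rule is the weaker one. One reservation remains. The baseline comparisons include outcome measures, but the article's list of baseline variables does not name A1c, so applying the rule to baseline A1c is a reading, although a natural one.

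Finally, 54%, 35% and 94% are complete-data figures at a single r. This stands, and the range is shown above. No correlation is given for blood pressure, LDL or behaviours, so the gain there cannot be quantified.

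**Conclusion.** The point holds as a matter of efficiency. The sample size is consistent with an unadjusted change-from-baseline comparison, the least efficient standard option at the protocol's own correlation. The stated adjustment rule leaves that loss in place unless the arms happen to differ. The trial is neither invalid nor underpowered.

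With complete data at 114 per group, equal SDs and a common design effect, adjustment raises power for 1.0 point from about 80% to about 94%. The change score's excess variance is 54% at the stated r, smaller at higher r, and about 46% under the planned imputation with 10% dropout. That the trend model carries the same loss is conditional on free group intercepts.

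**What to change.** In Data analyses, replace the conditional rule with unconditional adjustment in the first-year primary analysis, for A1c and for each other outcome measured at baseline. There are two equivalent routes in spirit: use the baseline value as a covariate with the 6- and 12-month values as outcomes, or keep baseline as a response and constrain the arms to a common baseline mean. Name the 12-month group difference as the effect.

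Limit the common-mean constraint to the randomised first-year comparison. It does not carry over to the 12-to-24-month maintenance and intensification hypotheses, whose starting point comes after treatment has acted.

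In Sample size calculation, keep 300 patients and restate the power and detectable difference for the adjusted analysis. Give the 2/(1 + r) dependence and the figure under return-to-baseline imputation.

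The cost is wording in two sections, settled before outcome data are seen. No extra patient, visit or measurement is needed.

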### Data analyses

Data will be analyzed for clinical effectiveness using intention-to-treat principles [32-34]. To represent dropouts in the analysis, missing data will be imputed using various approaches, such as “last value carried forward.” The Little and Yau “return to baseline” imputation rule, in which any gains over baseline levels dissipate upon dropout, will be used for primary analyses. Patients who share a single primary care physician (PCP) or health promoter (HP), might exhibit similarities that are not shared with patients attended to by other physicians. To address this, we will include random effects in the model for clinic site, PCP, and HP. We will include as predictors relevant care and treatment-related variability such as medication therapy intensifications and clinical encounter frequency.

We will test the hypothesis that A1c, blood pressure, and LDL-cholesterol levels will be lower and diabetes behaviors (including medication adherence) will be improved with patients receiving *Pharmacist+HP* compared with those receiving *Pharmacist* alone. Univariate comparisons between the two study groups with respect to outcome measures and covariates at baseline will be conducted using Chi-square tests for categorical variables, Kruskal-Wallis tests for ordinal variables, and linear mixed models for continuous variables. Non-normal continuous data will be transformed prior to linear model analyses. The baseline variables include demographic, therapy complexity, and health literacy data. If we find any between-group differences at baseline, we will adjust for this in our primary multivariate analyses by including relevant covariates.

We will also extend the usual analysis of crossover designs by including a longitudinal trend component in the first year. Thus, we can examine the time course (0, 6, and 12 months) as linear or quadratic over the first three measurements. This will allow us to investigate whether changes are made early, and at what rate they continue through the rest of the time period. This analysis permits the comparison of trends between *Pharmacist* and *Pharmacist+HP* conditions. In addition, we will regard participants as a random effect and will use Gaussian mixed-model estimations (SPSS MIXED command). We can then substitute treatment by period interactions for the carry-over effects, and the model can be reduced in a recommended sequence (first omit carry-over, then omit treatment, finally omit period).

The primary analysis of each outcome in the repeated measures design will be conducted in a general linear mixed model framework. In addition, SPSS MANOVA (for repeated measures) will be used to explore the simultaneous impact of the treatment on multiple correlated dependent variables, including the use of Roy-Bargmann stepdown F-tests and discriminant function analysis as post hoc tests to identify subsets of outcome measures affected [35]. SPSS MIXED will be used to explore patterned covariance structures such as compound symmetry and autoregression along with incorporating time-varying covariates, such as depression. MANOVA secondary analyses will explore the impact on results of inhomogeneous baseline variables. Exploratory subgroup analyses will determine which participants in the intervention group had the greatest improvement in outcomes, based on demographic factors, health literacy, and medication regimen. Group by time-trend interaction contrasts also will be used to explore different group trajectories of change. In addition, we will investigate the potential consequences of medication intensification (e.g., initiation of insulin) by evaluating changes in body mass index and severe hypoglycemia.

We will explore diabetes-related behaviors (including eating habits, physical activity, and medication adherence) as well as medication treatment intensification as alternative mediators using MPlus [36]. We will also test the hypothesis that diabetes behaviors and clinical outcomes will be maintained one year after phase-out of HP support. Finally, we will test the hypothesis that diabetes behaviors and clinical outcomes improved by adding HP support after one year of *Pharmacist* alone.

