*HP Activity* will be collected on a standardized worksheet completed after every participant contact (by phone and in-person). Information obtained will include mode, time, and content of contact, results of glucose or blood pressure self-monitoring, goals, and interventions. Additional information collected includes *PCP and Pharmacist Activity and Medication Changes.* The reconciled medication list from the medical chart will be used as data to evaluate medication changes and overall complexity of therapy. Intensification of therapy will be defined as the number of increases in the dosage of an antihypertensive agent, hypoglycemic agent, or insulin, or the addition of a new agent since the baseline visit [21]. Chart review will define the number of PCP and pharmacist encounters as well as the number of pharmacist- or physician-initiated medication changes. Chart review will also include information on actual medications prescribed for diabetes, hypertension and hyperlipidemia, co-morbid conditions, and diabetic complications.

*Clinical Outcomes* will be collected at four time points (0, 6-, 12-, and 24-months). Professional research staff will perform phlebotomy and measure blood pressure, weight and height. These staff will be blinded to participant group assignment. Hemoglobin A1c will be obtained via phlebotomy. The laboratory test has National Glycohemoglobin Standardization Program certification. Fasting lipid profiles will also be obtained via phlebotomy, including HDL, LDL, and triglyceride measurements. Both A1c and lipid profile results will be placed in the participant’s EMR. Height and weight measurements will be obtained to determine body mass index (BMI). A calibrated digital scale will measure weight. A height stadiometer will measure body height, with participants removing their shoes. Blood pressure measurements will be recorded on participants sitting down for at least five minutes, following standard procedure.

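### The effectiveness model conditions on post-randomisation therapy intensification, a named mediator, and on encounter frequency, so its group coefficient no longer estimates the total effect of adding health promoters

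*Protocol article*

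**What the plan says.** The Data analyses section of the protocol article opens with the principle: "Data will be analyzed for clinical effectiveness using intention-to-treat principles". It names the imputation rule for the primary analyses and the random effects for clinic site, physician and HP, and then adds: "We will include as predictors relevant care and treatment-related variability such as medication therapy intensifications and clinical encounter frequency". The hypothesis test of Pharmacist+HP against Pharmacist follows. Later the section says: "The primary analysis of each outcome in the repeated measures design will be conducted in a general linear mixed model framework". Nothing confines the care variables to a secondary or sensitivity analysis, and the Discussion says again that analyses will include medication changes.

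Four other places fix what these variables are:

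- **Study measures** counts intensification as dose increases "or the addition of a new agent since the baseline visit".
- **Identification, recruitment, and randomization of participants** says that randomisation "will occur after consent and completion of all baseline data collection".
- **Background** says of HP activities: "Such measures may improve medication adherence and support intensification to reach goals in blood sugar, blood pressure, and cholesterol".
- **Data analyses**, near its end, plans to explore diabetes behaviours "as well as medication treatment intensification as alternative mediators using MPlus".

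Encounters are described in Study measures as a chart-review count of physician and pharmacist contacts. The Pharmacists section lets the spacing of pharmacist encounters lengthen once participants reach their goals.

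**The concern.** The same variable is used in two incompatible ways. It is a path through which the intervention is expected to act, and it is also a covariate in the model that measures whether the intervention acts. The Objectives section asks how effective adding HP support is compared with pharmacist care alone, which is the total effect. Holding intensification constant blocks one path of that effect.

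It also introduces confounding that randomisation had removed. A1c results go into the medical record and pharmacists adjust therapy on response, so patients with poor control can be expected to receive more changes and more contacts. Comparing arms at equal intensification then compares patients who differ in prognosis. The coefficient would be reported under the intention-to-treat label without having that meaning, for every outcome analysed this way.

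**Working it through.** **Timing and role.** Intensification accrues from the baseline visit and allocation follows baseline collection. Apart from any change made in the gap between the two, the count is post-randomisation. The protocol calls it a mediator. For encounter frequency the text is less explicit. The chart-review count carries no stated time window, and a self-reported provider visit frequency is also collected at baseline. The follow-up count is the more plausible meaning, because the sentence speaks of variability in care and treatment.

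**The plan's own figure.** Inputs from Sample size calculation: difference 1.0, SD 1.8, cross-time correlation 0.30, ICC 0.02, cluster size 30, two-sided alpha 0.05, power 80%.

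- Design effect: 1 + (30 − 1) × 0.02 = 1.58.
- Variance factor for a change score: 2 × (1 − 0.30) = 1.4.
- n per group = 2 × [1.8 × (1.960 + 0.842) / 1.0]² × 1.4 × 1.58 = 50.86 × 1.4 × 1.58 ≈ 112.5, so 113.
- A t-based calculation gives 72.18 × 1.58 = 114.04.

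The stated 114 per group is reproduced. It is a sample size for the total difference of 1.0.

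**Conditioning on the mediator, no confounding.** Let a share s of the 1.0-point reduction pass through intensification. The documents do not give s, so it is assumed. By construction the adjusted contrast is 1.0 × (1 − s). For power, the effective n is 114 / 1.58 = 72.15 per group and the SD of change is 1.8 × √1.4 = 2.130. The standard error is 2.130 × √(2 / 72.15) = 0.355, and power is Φ(contrast / 0.355 − 1.960).

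| Assumed share s | Adjusted contrast | Power at 114 per group |
|---|---|---|
| 0 (total effect) | 1.00 | 80.5% |
| 10% | 0.90 | 72% |
| 25% | 0.75 | 56% |
| 50% | 0.50 | 29% |

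These powers ignore any fall in residual variance from the added predictor.

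**Conditioning on the mediator, with an unmeasured common cause.** Let U be a severity factor with variance 1 that raises intensification by 0.5 and A1c by 1.0 per unit. Let the HP arm raise intensification by 1, with other variance in intensification of 1. These values are illustrative. Within arms, U adds 0.5 / (0.25 + 1) = 0.40 to the slope of A1c on intensification. The size of the adjusted group coefficient becomes 1 − s + 0.40.

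| Assumed share s | Adjusted, no confounding | Adjusted, with U | Without adjustment |
|---|---|---|---|
| 10% | 0.90 | 1.30 | 1.0 |
| 25% | 0.75 | 1.15 | 1.0 |
| 50% | 0.50 | 0.90 | 1.0 |

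A simulation of 400,000 patients per setting agreed: 0.91, 0.76 and 0.50 without U, 1.31, 1.15 and 0.91 with U, and about 1.0 throughout without adjustment. The unadjusted contrast recovers the total effect in every setting. The adjusted one does not, and it misses in both directions.

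**The case against.** Several objections deserve weight.

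- **The sentence is not labelled primary.** Where the section names covariates for its primary multivariate analyses, they are baseline variables that differ between arms, and the sentence placing the primary analysis in a mixed model lists no covariates. A fuller plan may settle the list. This is fair. However, the sentence follows directly on the primary imputation rule and the random effects in the model, and nothing shown restricts it.
- **There is a motive.** The Discussion notes that other providers may change therapy outside study procedures. That is a reason to record and describe such changes. Adjusting for them still changes what is estimated.
- **A reader might infer that the protocol calls both variables mediators.** It does not; only intensification is named. For encounter frequency the supportable statement is that it is a care variable the intervention and the outcome may change.
- **A reader might infer that adjustment must shrink the effect, even to nothing.** The documents do not support that. The shrinkage in the first table follows from the assumed share, and a common cause can offset or reverse it. Shares near 100% also fit poorly with a design in which pharmacists manage medication in both arms and HPs add lifestyle and adherence support.
- **A reader might add time-varying depression to the charge.** The protocol does plan mixed models "along with incorporating time-varying covariates, such as depression", and Study measures classes depression as an intermediate variable. But that sentence describes exploration and does not specify the primary model.

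**Conclusion.** Wrong as written. The plan places a post-randomisation variable that it names as a mediator, together with a care variable likely to respond to treatment and outcome, among the predictors of its intention-to-treat effectiveness model. The resulting group coefficient does not estimate the total effect that the trial targets and is powered for. This rests on the protocol's own definitions and needs no assumed figures.

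The size of the error does does not follow from the documents. Under assumed mediated shares of 10% to 50%, a true 1.0-point effect would appear as about 0.90 to 0.50 without confounding, and as about 1.30 to 0.90 under one illustrative pattern of confounding. Direction is therefore not guaranteed. The sample size calculation is not itself in error.

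**What to change.** State in Data analyses that the primary effectiveness model for each outcome contains only treatment, time, baseline covariates and design factors (site, gender-by-ethnicity strata and the planned random effects). State that it excludes post-randomisation therapy intensification and encounter frequency. Move both to the MPlus mediation analysis already planned, or to secondary analyses labelled as conditional on post-randomisation care. Define encounter frequency by source and time window. Say that time-varying depression stays exploratory and does not enter the primary model.

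The cost is a change of wording. Data collection, visits and the target of 300 patients stay as they are, and the mechanism questions are still answered by the mediation analysis.
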